#### Primary outcomes

The primary outcome measures for this trial will be the feasibility of conducting a full-scale RCT to investigate a combined education and exercise program in the management of ankle OA. Feasibility will be evaluated using the following outcomes which will be assessed at the conclusion of the study:

Individuals’ interest in the study (number of responses to study advertisements);Number (percentage) of eligible individuals from interested individuals;Recruitment rate (average number of study participants enrolled per month);Consent rate (percentage of consented participants from eligible individuals);Participant adherence with allocated intervention (the number (percentage) of sessions attended and reasons for absence);Physiotherapist fidelity delivering the intervention, evaluated by observation by a researcher not involved in intervention delivery using the fidelity assessment from Davis et al. [29];Adverse events (number and type) recorded by the physiotherapist at each exercise session and from participant diaries;Completion rate (number (percentage) of participants who do complete the intervention and 8-week and 3-month outcome measures) and reasons for non-completion/drop out.

Based on previous feasibility studies [30] and exercise adherence in knee OA research [31] (in light of no previous studies investigating or reporting adherence in ankle OA), the criteria for determining feasibility of conducting a full-scale RCT using the current protocol are reported in Table 2.

**Table 2 Tab2:** Feasibility criteria for a future RCT

Outcome	Proceed	Proceed with caution	Do not proceed
Consent rate	> 50%	30–50%	< 30%
Participant adherence	> 60%	30–60%	< 30%
Intervention fidelity	> 60%	30–60%	< 30%
Completion rate of PROM ^a^ at 3 months	> 70%	50–70%	< 50%

*PROM *Participant-reported outcome measures

^a^Completion of at least severity of ankle pain and Global Rating of Change

To inform feasibility, credibility (how believable/logical the treatment is) and expectancy (expectations from treatment) will be evaluated using the Credibility/Expectancy Questionnaire [32]. This questionnaire has high internal consistency and test-retest reliability [32]. It will be completed at baseline, 1-week post-treatment commencement (after the first week of treatment has been completed), and 8-weeks post-treatment commencement (after the final treatment session for the education and exercise group).

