## Methods

### Study design

This feasibility study uses a mixed-methods approach with a central randomised parallel-group design and qualitative semi-structured interviews at trial completion. It follows the Standard Protocol Items: Recommendations for Interventional Trials (SPIRIT) guidelines [19], the CONSORT extension for randomised pilot and feasibility trials [20] and the Consensus on Exercise Reporting Template (CERT) [21]. Methodology and reporting of the semi-structured interviews will be guided by the Consolidated Criteria for Reporting Qualitative Studies (COREQ) [22]. The study is registered on the Australia New Zealand Clinical Trials Registry (ANZCTR; registration #: ACTRN12623000017628, registration date: 10 January 2023). Ethical approval has been obtained from The University of Queensland Human Research Ethics Committee (Approval #: 2018/HE002196) and all participants will provide informed consent prior to study participation.

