### Participants

Individuals will be recruited using a broad recruitment strategy that has been successfully used in previous ankle OA research [13]. We will use paid and unpaid advertisements on social media (e.g., Facebook, Twitter), websites (e.g., Weekend Notes, Arthritis Australia, Arthritis Queensland), newsletters (e.g., UQ Update), radio (e.g., 4BC), and electronic and physical noticeboards in the greater Brisbane area. Posters will be given to physiotherapy and inter-professional health clinics to post in their practices. Advertisements will use simple language and include a range of images to appeal to diverse individuals.

Formal sample size calculations are not applicable for feasibility studies. We chose a sample of 30 participants for feasibility of recruitment within the 1-year study period, while allowing observation of sample variability and any adverse responses. Individuals with ankle OA will be required to meet the following eligibility criteria for inclusion: (i) aged over 35 years; (ii) ankle joint pain on most days for the last three months; (iii) severity of ankle pain in the last week ≥ 3 out of 10 on an 11-point numerical rating scale (NRS) anchored with ‘no pain’ at 0 and ‘worst pain imaginable’ at 10; (iv) modified Kellgren & Lawrence scale (K&L) OA grade ≥ 2 at the subtalar and/or talocrural joints defined as the presence of osteophytes and/or joint space narrowing [23]; (v) committed to undergo the allocated treatment and undertake all follow up outcome measurements; and (vi) able to understand verbal and written English. Study exclusion criteria are: (i) health problems or pain elsewhere that are more concerning than that at the ankle; (ii) received exercise and/or education-based treatment for ankle OA in the last three months; (iii) previous ankle arthrodesis or total ankle replacement on the affected ankle; (iv) neurological, vestibular or systemic arthritic conditions; (v) receiving treatment for cancer; and (vi) inability to undertake radiographic evaluations (e.g. pregnancy) and/or participate in the treatment program.

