### Study procedures

The flow of participants through the study is shown in Fig. 1. Individuals who express interest in participating in the trial will complete a multi-stage screening process. First, they will complete a preliminary online screening survey and verbal phone screen to check eligibility. Second, individuals will undertake a comprehensive in-person physical examination by a registered physiotherapist to ensure that the individual’s ankle pain is arising from the ankle joint and not surrounding structures. Finally, individuals will undergo lateral and mortise view ankle x-rays at a radiology clinic to determine the presence of radiographic ankle OA at the subtalar and/or talocrural joints. Radiographs will be assessed by a researcher with radiology training to determine the stage of OA [23]. Interrater reliability of grading radiographic ankle OA severity in previous research from our group is substantial (Kappa: 0.69 (95% confidence intervals: 0.59, 0.79) [13]. Individuals who meet all eligibility criteria will complete informed consent documentation and baseline data collection with a research team member blinded to group allocation.

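### The Table 2 consent rate leaves people unwilling to accept allocation or follow-up out of its denominator, so it is biased upward by an unknown amount

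*Protocol article*

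**What the plan says.** Four places in the protocol article together determine the measure.

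- **Numerator and denominator** (Primary outcomes): "Consent rate (percentage of consented participants from eligible individuals".
- **Eligibility** (Participants, criterion v): a person must be "committed to undergo the allocated treatment and undertake all follow up outcome measurements". Criterion (iv) requires a radiographic grade of at least 2, so nobody is confirmed eligible before the x-ray.
- **Order of events** (Study procedures): "First, they will complete a preliminary online screening survey and verbal phone screen to check eligibility". Next, "individuals will undertake a comprehensive in-person physical examination by a registered physiotherapist". After that, "Finally, individuals will undergo lateral and mortise view ankle x-rays at a radiology clinic". Only then: "Individuals who meet all eligibility criteria will complete informed consent documentation and baseline data collection".
- **Use** (Primary outcomes, Table 2): "the criteria for determining feasibility of conducting a full-scale RCT using the current protocol are reported in Table 2". For consent the bands are above 50%, 30–50% and below 30%. The other three criteria are adherence, fidelity and completion of participant-reported outcomes at 3 months.

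Primary outcomes also lists the number of responses to advertisements, the number and percentage eligible among those interested, and the average number enrolled per month. None of these appears in Table 2.

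**The concern.** Consent rate is the only Table 2 criterion that concerns entry to the trial. A feasibility study would want such a rate to fall when people with ankle osteoarthritis are unwilling to take whichever arm they are given, or to attend follow-up. Here that unwillingness is itself a reason for ineligibility, so those people leave the denominator instead of counting against the rate. People who lose interest between the phone screen and the x-ray also never become confirmed eligible. What remains is consent among people who have declared commitment and completed every screening step.

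The percentage-eligible figure does not repair this. It combines people who are clinically unsuitable with people who are unwilling, and the two have different consequences for a full-scale trial. A proceed result on consent could therefore coexist with substantial reluctance that no progression criterion registers.

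**Working it through.** The plan has no calculated figure to reproduce. The 30 participants are a pragmatic choice (Participants), and the Discussion says the consent cut-offs draw on a cited feasibility study.

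**Step 1. What the defined rate needs in order to leave the proceed band.** Let D be the number of fully screened, declared-committed people who decline. With 30 enrolled, rate = 30/(30 + D).

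| D | Rate | Band |
|---|---|---|
| 3 | 30/33 = 90.9% | proceed |
| 10 | 30/40 = 75.0% | proceed |
| 29 | 30/59 = 50.8% | proceed |
| 30 | 30/60 = 50.0% | caution |
| 70 | 30/100 = 30.0% | caution |
| 71 | 30/101 = 29.7% | do not proceed |

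Leaving the proceed band takes as many late refusals as there are participants.

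**Step 2. Whether the criterion can still fail.** Treat the number of eligible people as fixed and each decision as independent, with an assumed post-screening consent probability p. The binomial chance of observing more than 50% is:

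- p = 0.7: 0.983 with 30 eligible people, 0.994 with 40.
- p = 0.5: between 0.43 and 0.50 for 30 to 40 eligible people.

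The criterion is easy to pass if declared commitment usually leads to consent. It still discriminates if it does not.

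**Step 3. How many omitted people would change the band.** Let W be the otherwise eligible people left out, either through criterion (v) or by withdrawing before the x-ray. The wider rate is 30/(30 + D + W). Take D = 3 (assumption); the defined rate is 90.9% whatever W is.

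| W | Wider rate | Band |
|---|---|---|
| 10 | 30/43 = 69.8% | proceed |
| 20 | 30/53 = 56.6% | proceed |
| 30 | 30/63 = 47.6% | caution |
| 40 | 30/73 = 41.1% | caution |
| 60 | 30/93 = 32.3% | caution |

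**Step 4. The same as a proportion.** Let c be consent after screening and w the share of otherwise eligible people willing to commit and complete screening. Then wider rate = c × w. With c = 95% (assumption):

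- It leaves the proceed band when w is at or below 0.50/0.95 = 0.526.
- It reaches do not proceed when w is below 0.30/0.95 = 0.316.
- w = 0.9, 0.8 and 0.6 give 85.5%, 76% and 57%, all still proceed.
- w = 0.5 gives 47.5% (caution); w = 0.3 gives 28.5% (do not proceed).

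The direction of the bias follows from the definition. Its size depends on W or w, which the article does not give.

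**The case against.** **Recruitment yield is reported elsewhere.** Responses, percentage eligible and monthly enrolment are also primary feasibility outcomes, and percentage eligible multiplied by consent rate gives the yield from interest to enrolment. This stands against any claim that the study says nothing about yield. It does not remove the concern, because none of these measures has a cut-off and percentage eligible does not separate unwilling from unsuitable people.

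**The criterion can fail.** A reader might infer that the consent criterion is passed automatically. The documents do not support that: stating commitment at screening is not signing consent, people can still decline at that point, and the article gives no expected consent rate.

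**The classification is partly inferred.** The article does not say when or how criterion (v) is assessed, or how withdrawals during screening are logged. The flow diagram is not visible in the text at hand, and a fuller protocol may hold logging rules. Counting the unwilling as ineligible is the literal consequence of the definition, not a stated rule. That limits certainty about practice but not about the definition.

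**Pre-x-ray withdrawals are not known to be eligible.** This stands. Some would have failed the radiographic criterion, so counting all of them gives a lower bound, not the true rate.

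**Consent timing.** A reader might see a contradiction between Study design, which says "all participants will provide informed consent prior to study participation", and the examination and x-ray that precede consent in Study procedures. None is shown. Study participation need not include screening, and consent is placed before baseline data collection. The consent documents are not in the text at hand, so a separate screening consent cannot be excluded.

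**Conclusion.** The point holds as a matter of definition. Because criterion (v) is part of eligibility, the Table 2 consent rate excludes the people whose refusal it would be expected to count, and it is biased upward. With 30 enrolled, leaving the proceed band would take at least 30 fully screened, declared-committed people declining.

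Whether this would change the progression decision cannot be determined from the article. Under an assumed 95% post-screening consent, it changes the band only if about 53% or fewer of otherwise eligible people are willing to commit and complete screening; above that, the result stays in the proceed band under either denominator. The 95%, the willingness shares and the counts D and W are all assumptions. This is a correctable weakness in one of four criteria that guide the decision, not evidence that the decision will be wrong.

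**What to change.** For the Table 2 consent rate only:

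1. Take criterion (v) out of the eligibility denominator. It may remain a condition of enrolment.
2. Count people who meet the other criteria but decline the allocation or the follow-up as eligible non-consenters.
3. Log voluntary withdrawals at each screening stage with the reason, separately from clinical ineligibility, and state at which stage criterion (v) is asked.
4. Report a sensitivity rate that adds those who withdrew before the x-ray, labelled as eligibility unconfirmed. If commitment is asked early, many decliners will appear only here, so the two rates should be read together as a range.
5. Apply the Table 2 cut-offs to the rate without criterion (v), and fix that choice before results are read. The denominator used in the feasibility study that supplied the cut-offs is not visible in the article, so the sponsor should confirm that they suit this one.

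The cost is a changed definition and a screening log with reasons by stage. The reported rate will be somewhat lower. Reasons not recorded at the time may not be recoverable, so the log should change as early as possible. The timing of consent need not change.

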The exercise sessions follow resistance training guidelines from the American College of Sports Medicine [24]. There will be two group exercise sessions per week over six weeks (a total of 12 exercise sessions, each of 1-hour duration) delivered by a trial physiotherapist (weeks 2–7 of the intervention). There will be 2–3 days of rest between exercise sessions. The exercise program will include aerobic exercise (i.e., stationary bike), exercises for foot/ankle muscle strength (i.e., resistance band and body weight exercises), compound lower limb exercises (i.e., step ups), postural control/balance training (i.e., standing on compliant surfaces) and gentle stretching (Table 1). Strengthening exercise sessions will be prescribed as two sets of 10–12 repetitions and 1 min rest between sets. Load (Theraband® and free weight resistance) will be individualised to study participants and will be an intensity that the participants can perform between a maximum of 10 and 12 repetitions with correct form/technique and a patient-acceptable level of pain (determined dichotomously with the question ‘Are your current symptoms acceptable, when you take your general functioning and your current pain into consideration?’). If the participant cannot perform 10 repetitions with correct technique or acceptable pain, a lighter load/resistance will be used. If the participant can perform more than 12 repetitions with good technique and acceptable pain, then a heavier load/resistance will be used. The load/resistance will be individually evaluated by the physiotherapist for each exercise and load will be progressed to maintain this workload. Each exercise repetition will consist of a 2-second concentric phase, 1-second isometric hold, and 2-second eccentric phase with a 1-second rest between repetitions. Each set will take about 60–70 s to complete with a total time under tension of 50–60 s per set (and 100–120 s per exercise). Exercises done unilaterally will be performed on both legs, with one set of the exercise performed on the unaffected side. If time does not allow performance of all exercises bilaterally, the resisted foot and ankle exercises will be omitted on the unaffected side. The detailed exercise program, including prescription and progressions, is outlined in Supplementary file 1.

**Table 1 Tab1:** The components of the exercise program

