**Warm up/ Aerobic exercise**	10 min of cycling on a cycle ergometer at a workload of ‘somewhat hard’ on the rate of perceived exertion (RPE) scale [25].
**Foot and ankle specific muscle strength (5 exercises)**	Five exercises for foot and ankle-specific muscle strength using body weight resistance or Theraband® resistance. The specific exercises are: calf raises (body weight resistance) and Theraband® resisted ankle dorsiflexion, ankle inversion, ankle eversion, and toe flexion.
**Compound lower limb muscle exercises (3 exercises)**	Three compound lower limb muscle strength exercises which include step up/downs (body weight resistance), squats/resisted knee extension (body weight or Theraband® resisted), and a pelvic lift/supine bridge (body weight resistance).
**Balance training (1 exercise)**	A standing balance exercise series with adjustment to base of support and addition of perturbations.
**Cool down**	Walking forward and backwards for 2–3 min at a self-determined comfortable pace, followed by gentle stretching of the ankle plantarflexors, quadriceps and hamstrings. Stretches are held for 30 s each.

Physiotherapists will record attendance; intensity (e.g., Theraband® colour or kilogram load), repetitions and sets for each exercise; patient-acceptable level of pain (acceptable vs. not acceptable); and any adverse events for each exercise session. If participants report an unacceptable level of symptoms following the previous exercise session, load will be carefully monitored and adjusted as needed.

Participants will not be given a home exercise program during the six weeks of group exercise classes. At the completion of the 6-week program, participants will be instructed to continue with the exercises twice a week at home (i.e., a home exercise program). A handout will be provided with instructions on how to complete each exercise, and when and how to progress.

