#### General advice intervention

Participants allocated to the general advice group will attend one 1-hour group session, where they will receive general information about OA (e.g., the importance of keeping active and tips on managing symptoms) based on online resources from Musculoskeletal Australia (*Understanding Osteoarthritis*) [26] and Arthritis Australia (*Information Sheet on Physical Activity*) [27]. They will be provided with the online resources in advance of their group session. The group session will be guided by a PowerPoint presentation to facilitate discussion about the information in the resources, and ample opportunity will be provided for participants to ask questions. Participants will receive a half-page handout of tips reinforcing the advice provided in the presentation and the contact details for the physiotherapist. No manual treatment or exercise prescription will be provided. Physiotherapists will record attendance at the general advice session. This is a similar treatment to other RCTs on musculoskeletal conditions and has been found to be acceptable to participants (based on recruitment rates, retention and participant feedback) [28].

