### Outcome assessment

Baseline participant demographic (e.g., sex, weight, height) and ankle OA (e.g., affected ankle, aggravating activities, and modified Kellgren & Lawrence scale (K&L) OA grade [23]) data will be collected. Participant-reported outcome measures will be collected at baseline, 8 weeks and 3 months post-commencement of the intervention using an online survey platform (Qualtrics). Follow up data will be collected on all participants, including those who deviate from or discontinue their treatment allocation.

Participants will complete weekly diaries throughout the 3-month study period to record any adverse events in relation to their ankle or general health, any treatment they sought and any changes to medication they take for their ankle. Diaries will be given to participants at their first treatment session, with instructions to email a photo of the diary to their physiotherapist weekly (or to return it at the exercise session for those in the combined education and exercise intervention). Participants will receive a weekly reminder from their physiotherapist to submit the diary. Use of interventions outside of the study will be recorded as type (e.g., medication use, physiotherapy), number and percentage.

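### Adverse events have two recording sources in the exercise arm but only the diary in the advice arm, and a randomised participant who never attends gets no diary

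*Protocol article*

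**What the plan says.** All references are to the protocol article. Its Primary outcomes section defines the adverse-event outcome from two sources: "Adverse events (number and type) recorded by the physiotherapist at each exercise session and from participant diaries".

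- **Exercise arm, sessions.** Under Education and exercise intervention, "There will be two group exercise sessions per week over six weeks", in weeks 2 to 7. The physiotherapist notes "any adverse events for each exercise session", alongside attendance, load and acceptability of pain.
- **Advice arm, sessions.** Under General advice intervention, participants "will attend one 1-hour group session". The record described there is attendance: "Physiotherapists will record attendance at the general advice session".
- **Both arms, diary.** Under Outcome assessment, "Participants will complete weekly diaries throughout the 3-month study period to record any adverse events in relation to their ankle or general health". On issue and return: "Diaries will be given to participants at their first treatment session, with instructions to email a photo of the diary to their physiotherapist weekly". The exercise arm may instead hand the diary in at a class. A weekly reminder from the physiotherapist goes to participants in both arms.
- **Follow-up.** The same section promises follow-up data on all participants, including those who deviate from or stop their allocated treatment. It times the 8-week and 3-month assessments from the start of the intervention.
- **Analysis.** Under Data and statistical analysis, the primary outcomes are presented descriptively. Table 2 sets no adverse-event threshold.

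**The concern.** An adverse event in the exercise arm can enter the record by two routes while classes run. In the advice arm it can enter by one. Even if the true event rates are equal, the arm with the additional route will tend to show more events unless the diary already captures everything. Someone comparing the two counts could then read a recording artefact as a harm of exercise.

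A second gap lies in who gets a diary. Because "Diaries will be given to participants at their first treatment session", a person who is randomised but never attends has neither a diary nor a session record. The general promise of follow-up names no other way of collecting adverse events. Its timepoints are also counted from a treatment start that such a person does not have.

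At stake is the reading of a listed primary feasibility outcome. The Participants section also says that the sample of 30 was chosen partly to allow adverse responses to be observed. The study is meant to show whether a full-scale trial can use the current protocol, so the asymmetry could carry over into a trial that does compare the arms.

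**Working it through.** **Recording occasions.** 2 sessions per week × 6 weeks = 12, which matches the article's own total. Physiotherapist adverse-event recording occasions described: 12 in the exercise arm, 0 in the advice arm.

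**Model for relative ascertainment.** The article gives no capture rates, so these are assumptions. Let c be the probability that the diary captures an event and s the probability that session recording captures it. Take the two as independent and the true rates as equal in the arms and constant over time.

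- Advice arm, all weeks: c.
- Exercise arm, weeks 2–7 (6 weeks): e = 1 − (1 − c)(1 − s).
- Exercise arm, other weeks: c.
- Ratio in weeks 2–7: e / c.
- Ratio over the 3-month period, taken as 13 weeks: (6e + 7c) / (13c).

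**With s = 0.80:**

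| Diary capture c | e | Ratio, weeks 2–7 | Ratio, 13 weeks |
|---|---|---|---|
| 0.50 | 1 − 0.5 × 0.2 = 0.90 | 0.90 / 0.50 = 1.80 | (5.40 + 3.50) / 6.50 = 1.37 |
| 0.80 | 1 − 0.2 × 0.2 = 0.96 | 0.96 / 0.80 = 1.20 | (5.76 + 5.60) / 10.40 = 1.09 |
| 0.90 | 1 − 0.1 × 0.2 = 0.98 | 0.98 / 0.90 = 1.09 | (5.88 + 6.30) / 11.70 = 1.04 |
| 1.00 | 1.00 | 1.00 | 1.00 |

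Varying s from 0.50 to 0.90 at c = 0.50 gives 1.50–1.90 in weeks 2–7 and 1.23–1.42 over 13 weeks. At c = 0.90 it gives 1.06–1.10 and 1.03–1.05.

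**Non-starters.** With 30 participants randomised 1:1, an arm has about 15. One non-starter is 1 / 15 = 6.7% of an arm with no described adverse-event route. If a proportion p never starts (assumed), the chance of at least one among 30 is 1 − (1 − p)^30: 60% for p = 3%, 79% for p = 5% and 96% for p = 10%.

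**After equalising.** If both arms are described from the same sources, with the same schedule, start point and capture, the ratio at equal true rates is c / c = 1.00, and every randomised participant has a route.

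**The case against.** The strongest reply is that no between-arm comparison of adverse events is planned. The outcome is number and type, analysed descriptively. By-group summaries are specified only for the variability of participant-reported and physical outcomes. Adverse events are not among the four Table 2 criteria that guide the decision to proceed. This stands, and it limits the weight of the point. It does not remove it: under Data management, adverse events are stored with coded allocation, so counts by arm can be produced, and descriptive presentation does not cure unequal ascertainment.

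The size rests on assumed capture rates. Weekly reminders go to both arms and should raise diary return. Independence is also doubtful, because the physiotherapist who records session events also receives and prompts for the diary. With maximal overlap between the two sources at s = 0.80, the weeks 2–7 ratio falls from 1.80 to 0.80 / 0.50 = 1.60 at c = 0.50, and from 1.20 to 0.80 / 0.80 = 1.00 at c = 0.80. The direction stands; the size is illustrative only.

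Non-starters may be few, since eligibility requires commitment to the allocated treatment. That is fair, but the article does fix when diaries are issued, and on that rule a non-starter receives none.

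Three stronger readings do not hold:

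- **That the asymmetry distorts the decision to proceed.** Adverse events carry no threshold there.
- **That co-intervention use is under-reported in the advice arm.** Nothing shows poorer diary return in that arm. The abstract also lists co-intervention use among the participant-reported outcomes with follow-up at 8 weeks and 3 months, so the diary may not be the only source.
- **That non-starters are lost to the study.** Follow-up is promised for everyone; what is missing is a described adverse-event route.

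Session recording itself is sensible monitoring and should stay.

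**Conclusion.** The point holds in a limited form. As written, the plan gives the exercise arm a second adverse-event source that the advice arm lacks, and ties the only shared source to attending a first session. Counts by arm would tend to be relatively higher in the exercise arm. The ratio from recording alone is about 1.2–1.8 in weeks 2 to 7 and about 1.1–1.4 over roughly 13 weeks. Those ranges assume equal true rates, 80% session capture, 50–80% diary capture and independence. They move towards 1 as diary capture becomes complete or the two sources overlap. The effect is on how a descriptive primary outcome is read, not on a test or a progression rule. This is an inexpensive improvement, not a flaw that invalidates the study.

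**What to change.** 1. Issue the diary to every participant at baseline or randomisation, with the same electronic return route in both arms.
2. Add one identical adverse-event question to the existing 8-week and 3-month online surveys in both arms.
3. Report adverse events by source and by arm, with the number of diaries returned. Keep session recording, but show those events separately as exercise-arm data.
4. Base any between-arm description on the sources common to both arms. State the caveat that exercise participants may tell the physiotherapist of an event and not write it down, which would bias a common-source comparison the other way.
5. For participants who never start, time the diary and surveys from their first scheduled session.

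The cost is wording and diary logistics, slightly longer surveys, and fewer events in any between-arm table. No extra visits or staff are needed.

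### Adverse events are summarised as a bare count, the advice arm's only stated source is the weekly diary, and diary return is not a feasibility outcome

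*Protocol article*

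**What the plan says.** The *Outcome assessment* section sets up the diary: "Participants will complete weekly diaries throughout the 3-month study period to record any adverse events". It also collects "any treatment they sought and any changes to medication they take for their ankle". Diaries are emailed weekly to the physiotherapist, with an alternative for one arm only: "or to return it at the exercise session for those in the combined education and exercise intervention". There is one safeguard against non-return, and it applies to both arms: "Participants will receive a weekly reminder from their physiotherapist to submit the diary".

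Under *Primary outcomes*, adverse events are one of eight feasibility outcomes, defined as: "Adverse events (number and type) recorded by the physiotherapist at each exercise session and from participant diaries". Outside treatment is summarised under *Outcome assessment*: "Use of interventions outside of the study will be recorded as type (e.g., medication use, physiotherapy), number and percentage". The denominator of that percentage is not stated.

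Contact with the physiotherapist differs by arm. For exercise: "There will be two group exercise sessions per week over six weeks (a total of 12 exercise sessions, each of 1-hour duration", in weeks 2–7, and the physiotherapist notes "any adverse events for each exercise session". For general advice there is one session, and the only record mentioned is attendance.

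The completion outcome covers the intervention and the 8-week and 3-month measures. Table 2 requires only pain severity and Global Rating of Change at 3 months. Neither mentions diaries.

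**The concern.** A number of adverse events can be interpreted only if one knows how much follow-up produced it. Here the number depends partly on whether diaries arrive, and nothing listed as an outcome measures that. A small count could show that little happened or that few diaries came back, and the stated summary does not tell these apart.

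Ascertainment is also unequal by design. The exercise arm has a second source of adverse events and an easier route for handing in diaries during six of the roughly 13 weeks. The advice arm has neither. Any shortfall in diaries would therefore tend to remove more events from the advice arm and make exercise look relatively more harmful.

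A further cost falls on the purpose of the study. A feasibility trial should show whether its data collection works. As written, all four rows of Table 2 could be met while the diary, which is the main route for adverse events in one arm and the only detailed route for outside treatment in both, had largely failed, and no listed outcome would reveal it.

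**Working it through.** The plan gives no figure to reproduce. The working shows how far an unadjusted count could mislead.

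**Inputs from the article**
- 30 participants randomised 1:1, so about 15 per arm (*Participants*; *Study procedures*).
- Weekly diaries for 3 months. The number of weeks is derived: 365.25/4/7 = 13.04, so about 13.
- Exercise sessions in weeks 2–7, which is 6 weeks. The other 7 weeks are week 1 and weeks 8–13.

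**Diaries due**
- 30 × 13 = 390 in total, or 15 × 13 = 195 per arm.
- If 80% were returned overall, 390 × 0.20 = 78 would be missing.

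**Assumptions (none is in the article)**
- The true weekly event rate is the same in both arms and constant over time.
- A fraction r of diaries is returned in all 13 advice-arm weeks and in the 7 exercise-arm weeks outside weeks 2–7.
- Session records plus in-person return capture every event in the exercise arm in weeks 2–7.

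**Share of events captured**
- Advice arm: r.
- Exercise arm: (6 + 7r)/13.
- Apparent exercise:advice ratio: [(6 + 7r)/13] / r.

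| Assumed r | Advice arm | Exercise arm | Ratio |
|---|---|---|---|
| 90% | 90% | 12.3/13 = 95% | 1.05 |
| 80% | 80% | 11.6/13 = 89% | 1.12 |
| 70% | 70% | 10.9/13 = 84% | 1.20 |
| 60% | 60% | 10.2/13 = 78% | 1.31 |
| 50% | 50% | 9.5/13 = 73% | 1.46 |

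The true ratio is 1.00 in every row. Counting 3 months as 12 weeks changes little: (6 + 6r)/12 divided by r gives 1.33 at 60% and 1.50 at 50%.

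**Bound on the session-week mechanism**
The table already gives the exercise arm full capture in its six session weeks, so its ratios are the largest that this route can produce at each r. An overall return of 90% against 60% would give 0.90/0.60 = 1.5, but with 60% return in the other 7 weeks the exercise arm would need (0.90 × 13 − 0.60 × 7)/6 = 7.5/6 = 125% in weeks 2–7. For 90% against 50%, a ratio of 1.8, it would need (11.7 − 3.5)/6 = 137%. Neither is possible without some further difference between arms that the article does not describe.

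**The case against.** The strongest objection is that a reader might infer that a week without a diary is counted as a week without an event. The article states no such rule. It says that primary outcomes will be presented descriptively, which leaves room to report how many diaries came back. *Data management* enters diaries and adverse events by participant code and coded allocation, so a tally is possible. Handling of missing diaries may also sit in a fuller protocol or analysis plan that is not shown. This stands: zero-imputation cannot be attributed to the plan.

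Several other limits stand too.
- Adverse events do not come from diaries alone, because the exercise arm has session records. This narrows the dependence on diaries but is also the source of the imbalance.
- Outside treatment is not only a raw count, because a percentage is planned. *Concurrent treatments* also asks participants to report interventions used, although the secondary outcomes describe no survey item for it.
- No formal comparison of adverse events between arms is planned, and Table 2 has no adverse event row. An under-count cannot change the stated proceed classification.
- The weekly reminder covers both arms and should limit non-return.

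What the objection does not remove is that the choice of feasibility outcomes and the form of the adverse event summary are fixed in this article. The reminder encourages return but does not measure it.

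**Conclusion.** The point holds as a cheap improvement. Adverse events are a primary feasibility outcome with no stated denominator, their ascertainment is richer in the exercise arm, and diary return is not among the outcomes that define feasibility. Under-counting is possible and would tend to be greater in the advice arm.

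The size depends on return rates that the article does not give. Under the stated assumptions the spurious ratio is small at high return (1.05 at 90%) and material at low return (1.31 at 60%, 1.46 at 50%). Different true rates, imperfect capture at sessions, or unequal return outside weeks 2–7 would change these values.

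The documents do not support saying that the plan treats missing diaries as absence of harm, or that the decision to proceed would be wrong as a result.

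**What to change.** - Log each due diary as returned or not. Count as due every follow-up week of every randomised participant. Diaries are handed out at the first treatment session, so someone who attends none may not receive one.
- Add returned/due, by arm and by period (weeks 1–7 and weeks 8–13), to the feasibility outcomes.
- Report diary adverse events per returned diary-week, separately from those recorded at exercise sessions.
- Give the percentage using outside treatment among participants with returned diaries, and state that denominator.
- State that unreturned weeks are missing, and that raw counts will not be interpreted between arms.

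The cost is one extra spreadsheet column, since the physiotherapist already sends a weekly reminder, and a few sentences under *Outcome assessment* and *Primary outcomes*. The downside is one more reported figure, which may be unflattering.
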